#### 4.2.2. Other Variables

(1) Sociodemographic characteristics

Participants and their parents will complete questions on sociodemographic characteristics, such as age, school grade and class, gender, full postal address and children´s bicycle ownership.

(2) Cycling knowledge and skills

The knowledge about route safety rules, cycling hand signalling, and circulation will be self-reported by participants at classroom, completing a 20-questions test with multiple-choice answers [56]. A final score will be obtained with the number of correct answers.

The cycling skills of the participants will be measured during the second and third session of the school-based intervention using two ad hoc observational checklists completed by the cycling teacher after every participant´s performance indicating a dichotomic answer (*yes/no*). The observational checklist for the second session on cycling traffic-free includes 18 skills grouped in 6 categories (i.e., starting off, pedalling and changing gears; turning right; turning left; performing zig-zag; breaking; unexpected turning) and the observational checklist for the third session on cycling on-road includes 32 behaviours grouped in 7 items (i.e., starting from side of route (kerb) and starting off; overtaking and lane changing; turning left to a secondary street; turning right to a secondary street; turning left to a main street; turning right to a main street; crossing a roundabout), and both includes a final item about the participant´s general behaviour. A final score will be obtained by every participant of 0–18 points in the first checklist and 0–32 points in the second checklist. For safety reasons, the participants that will not achieve at least 10 points and six compulsory behaviours related to perform safety right and left turns in the first checklist during the traffic-free cycling lesson, will not be invited to participate in the next on-road cycling session. The checklist is also available elsewhere [56].

(3) Perceptions

Participants will complete questions about their perceived barriers to ACS using the previous valid and reliable BATACE (*BArreras en el Transporte Activo al Centro Educativo*) Scale in Spanish adolescents [64]. It is an 18-item scale related to the environment/safety and planning/psychosocial factors. The final variable to analyse will be an average score ranging from 1 to 4 (strongly disagree to strongly agree), for every item and for every factor.

(4) Psychosocial

Participants will complete two questionnaires about the psychosocial SDT-related variables of autonomy, competence, and relatedness satisfaction in ACS and, motivation for ACS.

The basic psychological needs of autonomy, competence, and relatedness satisfaction in ACS will be determinate using the valid and reliable *Basic Psychological Need Satisfaction in Active Commuting to and from School* Scale [65]. It is a Spanish version adapted from the *Basic Psychological Needs in Exercise Scale to PE* [73] to the domain of ACS. The scale consists of 12 items that assess: autonomy satisfaction, competence satisfaction, and relatedness satisfaction in ACS, introduced by the question *“What do you think about your usual mode of commuting to and from school?”* Students’ responses to the scale will be performed on a 5-point scale ranging from 1 to 5 (strongly disagree to strongly agree).

The motivation for ACS will be measured using the valid and reliable *Behavioural Regulation in Active Commuting to and from School (BR-ACS)* questionnaire [66]. It is a Spanish version adapted from the *Behavioural Regulation in Exercise Questionnaire-3* [74] to the behaviour of ACS. This new scale contains 6 factors and 23 items assessing: intrinsic motivation, integrated regulation, identified regulation, introjected regulation, external regulation, and motivation. Responses to the statement “I go or would go to and from school walking or cycling because …” will be recorded on a 5-point Likert-type scale ranging from 0 to 4 (not true for me to very true for me).

(5) Anthropometric

Anthropometric and body composition will be assessed following the recommendations of the International Society for the Advancement of Kinanthropometry [75]. A digital platform and a height meter will be used to assess weight and height. To assess the waist circumference, a non-elastic tape measure will be used. Body mass index will be calculated as the weight in kilograms divided by the square of the height in meters. More information is described elsewhere [58].

(6) Family socioeconomic status

The family socioeconomic status will be self-reported by adolescents using several questions from the Family Affluence Scale II [76] and by parents using several questions from the Family Affluence Scale (FAS) III [67]. In addition, the parents will self-report the familiar income and the parental highest educational level [69].

(7) Parental perceptions

The perceived barriers to allow their children to commute actively to school will be assessed using the previous valid and reliable PABACS (Parental Perception of Barriers towards Active Commuting to School) questionnaire in Spanish children and adolescents [68]. It is a 23-item questionnaire categorized into 3 scales (general, walking, and cycling barriers) designed to determine the main parental barriers. The final variable to analyse will be an average score ranging from 1 to 4 (strongly disagree to strongly agree), for every item and for every scale.

(8) Peer social support

The peer social support to ACS will be self-reported by parents using a question from the School Travel and Safety survey used in the “Walk to School” study among American children [5]. The question will be: *“How often do other people in the neighbourhood walk or cycling with children to/from school?”* Response options: *everyday, a few times a week, a few times a month, a few times a year, or never*. The final variable to analyse will be the percentage of parents at a given school who will respond “everyday” or “a few times a week”.

(9) School characteristics

The student enrolment will be a measure of the school size (i.e., the number of students enrolled in the school during the year of participating in the current study). The school socioeconomic status will be calculated in accordance to previous studies [77,78]. Then, school neighbourhoods will be objectively analysed and classified as high or low socioeconomic status based on a Geographic Information System. The school engagement (to define its implication within the study since it might influence the intervention effects obtained in the study) will be 3 study reporting 3 variables per school: “teacher’s engagement” (i.e., the average of the researcher staff perceptions of the teacher’s engagement from all the classes); “student’s engagement” (i.e., the average of the researcher staff perceptions of the student’s engagement from all the classes); and “school’s engagement” (i.e., the average of the previous teachers and student’s engagement).

(10) City characteristics

The population density (number of inhabitants per city area in km^2^ -inhabitants/km^2^-) will be obtained from the Ministry of Finance and Public Administration of Spain, using the available data closest to the data collection year in each city. The city income from the data collection year will be obtained from the Spanish Public Tax Agency.

(11) Home–school distance

The distance between home and school will be objectively calculated in two ways. A first way previously used [79] will be to calculate the shortest walking network path between the home and the school of each participant using Google Maps™ software. A second way will be obtained combining GPS and Geographical Information System data to establish the real route between home and school. In both cases, the familiar postal address, that will be self-reported by participants and their parents, and the school’s postal address will be used as reference points.

(12) Home and school neighbourhoods

The length of the cycling lane network in a school area within a 5.1 km street-network buffer will be calculated using a Geographical Information System, both for the school´s intervention groups and control groups. The cut point of 5.1 km is stablished considering the threshold distance for cycling to school among Spanish young adults [80]. In addition, the availability of bicycle racks at the schools (or near the main entrance) will be required to the school staff. Cycle lanes data have been obtained through OpenStreetMap (OSM), which data are available for free use under the OSM Open Database License (ODbL).

(13) Weather

Weather variables will be obtained from the National Weather Data Bank, an open source with climatological information recorded by observatories throughout the country. We will include data on temperature (maximum, minimum, and mean), total rainfall, and mean wind speed, collected by the weather station nearest to each school during each of the five weekdays, and the weekend prior to the Student questionnaire completion, in both baseline and follow-up measurements.

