The 7 h intervention has four sessions that will be implemented during PE sessions over a period of one month (1 weekly session). An expert teacher in cycling in an urban context will lead all the intervention sessions, and the PE teachers will attend to learn and support the sessions. The sessions are described below (see Figure 4):

(1) Theoretical session (60 min—first week): theoretical session in the classroom to provide the participants a first step in the concept of cycling as a mode of commuting in the city. The content will include: awareness about the benefits and usefulness of cycling as a mode of commuting, knowledge about road safety rules for cycling, knowledge about cycling safety equipment for both the rider and the bicycle, and cycling hand signals in urban context.

(2) Closed circuit session (120 min—second week): practical session on the school grounds to learn or improve the fundamental cycling skills needed to ride the bicycle safely. The participants will practice how to fit the helmet and check the bicycle before cycling, as well as the fundamental cycling skills through 10 activities and a cycling circuit. The contents will include: correct helmet fitting, bicycle safety check before the ride, and the fundamental cycling skills of starting off and pedalling, breaking safely, changing gears, and hand signals to change directions.

(3) Urban circuit session (120 min—third week): practical session in urban context on-road traffic to transfer the previously learnt cycling knowledge and skills. The participants will learn advanced cycling skills on-road and will use the previously learnt cycling skills in new, uncertain, and modifiable on-road situations exposed to urban traffic. The content will include: starting from side of road (curb), stopping on side of road (kerb), overtaking a parked or slower-moving vehicle, lane changing, turning right and left, and crossing a roundabout.

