Regarding the methodology, the sessions will promote the student´s participation and the language used for communication will be inclusive and adapted to them. Active participation of the students will be promoted through questions, encouraging dialogue, and providing meaningful individual and group feedback. The urban circuit (third session) will be supported by expert cycling instructors and school teachers, to accomplish the ratio of 2 adults (i.e., one cycling instructor and one schoolteacher) per 10 participants.

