The following covariables will be included in the regression models: children´s age and gender, date of birth, school grade and name, class, bicycle ownership, parent´s age and gender, weight, height, waist circumference, body mass index, family income, parental educational level, student enrolment, school socioeconomic status, school engagement, population density, city income, distance home-school, cycling lane length, bicycle racks and weather.

Considering that our main aim is to assess real-world effectiveness of the intervention, we will conduct a primary analysis based on an intention-to-treat principle (in which we will analyse participants according to the groups originally assigned). Then, we will conduct a sensitivity analysis per protocol (in which we will exclude participants who did not complete the intervention and/or did not reach a minimum of 75% of attendance).

Analyses will be conducted using the Statistical Package for Social Sciences (SPSS, v. 25.0, IBM SPSS Statistics, IBM Corporation), and the level of significance will be set at *p* < 0.05.

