In the search for balance, several pragmatic adaptations will be made to conduct the research in “real-world” scenarios (such as school) where decisions need to be made on how to best conduct the study with the limited amount of time and resources that researchers may have [82]. In the PACO study, these adaptations pertain to the study design, implementation, and evaluation. Firstly, the school teachers will be able to choose the participating class groups, within the same grade. The pilot study and several consultations with school teachers showed that teachers want to choose the participating class and this will increase their involvement in the intervention. Secondly, all high schools in the three participating cities will be included in the random selection processes and then, the chosen schools will be invited to participate. Time limitations do not allow to visit each school for this purpose, and emails to schools have been previously sent (in previous studies of the research group) and they have not been answered because of high workload. Consequently, we will include all the schools in the random process to guarantee that everyone has the same likelihood to be selected. Thirdly, the intervention includes 4 sessions during a 1-month period. Research staff will offer the option to teachers of spreading the 2 h lesson of the 2nd and 4th session in two 1 h sessions using the normal PE schedule. In Spain, the national educational system in secondary schools mandates 2 h per week of PE. Fourthly, regarding the organization of the academic year in 3 trimesters, the study will be implemented in full trimesters to avoid holiday times, including the assessments. Finally, the cycling skills will be assessed by the teacher using a checklist twice during the intervention, simulating real evaluation conditions. However, safety (e.g., to avoid risky activities where children perform skills that they have not learned yet) and time limitations (e.g., lack of more PE sessions to enlarge the intervention), will prevent the cycling skills assessment being carried out at baseline and follow-up, respectively. To summarize, doing research in schools is important to prevent unhealthy behaviours and related beliefs common in our society. Achieving a balance between the scientific requirements of randomized designs and the constraints imposed by real world circumstances is necessary to improve the quality of research conducted in educational settings [83]. It is also consistent with recent calls to achieve a balance between the established evidence-based pathway and a practice-based evidence pathway, and for a more nuanced approach to appraising the utility of diverse types of evidence [84].

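### As described, the minimum bar for the on-road session names no compulsory braking behaviour, although braking is a separately scored category

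*Protocol article*

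**What the plan says.** Section 4.2.2, under cycling knowledge and skills, describes a checklist of 18 yes/no skills that the cycling teacher completes for each pupil in session 2, scored 0 to 18. Its six categories are "starting off, pedalling and changing gears; turning right; turning left; performing zig-zag; breaking; unexpected turning" (the article spells braking as *breaking*). Safety is given as the reason for a minimum bar. Pupils who "will not achieve at least 10 points and six compulsory behaviours related to perform safety right and left turns in the first checklist" "will not be invited to participate in the next on-road cycling session".

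Section 3.2 says that session 2 covers "the fundamental cycling skills of starting off and pedalling, breaking safely, changing gears, and hand signals to change directions". In session 3, pupils "will use the previously learnt cycling skills in new, uncertain, and modifiable on-road situations exposed to urban traffic". That session is supervised at a "ratio of 2 adults (i.e., one cycling instructor and one schoolteacher) per 10 participants".

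No other section adds a braking requirement for entry to session 3.

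**The concern.** The bar is the only written competence criterion that decides which 14- to 15-year-olds are kept out of traffic. It has two parts: a total score, which can be reached in many ways, and a compulsory set, which cannot be traded off. Only the compulsory set guarantees that a given skill was shown. As described, that set concerns right and left turns. Braking has its own category, so it counts only towards the total, where points from elsewhere can replace it.

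At stake is participant safety in one session. A pupil who showed no braking skill in session 2 could satisfy the written rule, and holding that pupil back would then rest on the instructor alone. The seven groups of the on-road checklist contain no braking category either. Session 2 is thus the only place where the article describes braking as scored in its own right.

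**Working it through.** **Inputs from the article.** Checklist: 18 yes/no items, score 0 to 18, six categories, braking separate from turning right and turning left (Section 4.2.2). Bar: at least 10 points and six compulsory turning behaviours (Section 4.2.2). Session lengths: 60, 120, 120 and 120 minutes (Section 3.2).

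**Input not given.** The number of braking items, called *b* here.

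**Step 1: points the bar leaves free.** The six compulsory items give 6 points. The remaining 10 − 6 = 4 points can come from any of the other 18 − 6 = 12 items.

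**Step 2: best score with every braking item failed.** This is 18 − *b*. The bar can be met if 18 − *b* ≥ 10, that is *b* ≤ 8.

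| *b* | Maximum score with no braking item | Bar of 10 reachable? |
|---|---|---|
| 1 | 17 | yes |
| 3 (even split, 18/6; an assumption) | 15 | yes |
| 8 | 10 | yes |
| 9 | 9 | no |

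**Step 3: is *b* ≥ 9 plausible?** The first category alone names three skills. Assume one item for each of them and at least one for zig-zag. Assume also that the six compulsory items all lie in the turning categories. Then *b* is at most 18 − 6 − 3 − 1 = 8, so the bar stays reachable without braking. This is a plausibility argument; the item list is not shown.

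**Step 4: other readings of the rule.** If the 10 points were meant in addition to the six compulsory ones, the bar would be 16 of 18, and a pupil with no braking item would pass only if *b* ≤ 2. The natural reading is a total of 10 that includes the six. The sentence could also be read as keeping out only pupils who fail both conditions, which would make the bar looser.

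**Step 5: what missing session 3 does to attendance.** The four sessions sum to 60 + 120 + 120 + 120 = 420 minutes, which reproduces the stated 7 hours. Without session 3, a pupil keeps 300/420 = 71.4% by time, or 3/4 = 75% by session count.

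**The case against.** The strongest objection is that the item wording cannot be seen. The article refers to another source for the checklist and gives only category labels and a short description of the compulsory set. A compulsory turning behaviour may already include slowing or stopping before the turn, and a condensed article may leave such detail out. This stands as a limit on certainty. It does not remove the point, because the article does state the rule, says what the compulsory behaviours concern, and puts braking in a category of its own.

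Second, the choice of compulsory skills is a matter for cycling instructors, and turns fit the session: four of the seven on-road groups are turns. That is fair. However, session 3 also includes stopping at the kerb, so braking is not peripheral to it.

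Third, there are real safeguards. An expert in urban cycling leads all sessions, the cycling teacher scores each pupil after observing the performance, and the on-road ratio is 2 adults per 10 pupils. The bar is a minimum for exclusion, so a pupil who meets it can still be held back. This stands, and it is why the severity is low.

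A reader might also infer that the plan contradicts itself, because the Discussion gives "to avoid risky activities where children perform skills that they have not learned yet" as a safety reason. The documents do not support that. The remark explains why skills are not tested at baseline, before any teaching, whereas the bar applies after braking has been taught in session 2.

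**Conclusion.** The point holds as a low-severity, cheap improvement for participant safety. Followed as described, the bar can be met by a pupil who fails every braking item, provided there are 8 or fewer such items. The conclusion rests on three assumptions: the 10 points include the six compulsory ones, no compulsory turning item already contains braking, and *b* is at most 8.

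Two stronger readings are not supported. One is that pupils who cannot brake will in fact be sent into traffic. The arithmetic shows only that the written rule permits it, and a pupil who performs all six turning behaviours and gains four further points may rarely fail all braking items. The other is a count of pupils affected. The article gives neither the number of braking items nor any pass rates, so no estimate is possible.

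No outcome, sample size, power or error rate is affected.

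**What to change.** In Section 4.2.2, add the already scored braking item or items to the compulsory set and word the rule so that both conditions are required. For example: *Pupils will be invited to the on-road session only if they score at least 10 of 18 points and show all compulsory turning and braking behaviours.* If a compulsory turning item already covers braking, saying so in that sentence is enough.

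The cost is one sentence and a change to the compulsory marks on the checklist, with no new measurement. The downside is that a few more pupils may miss session 3. They would keep 75% of sessions but 71.4% of the time, and Section 6 removes from the per-protocol analysis "participants who did not complete the intervention and/or did not reach a minimum of 75% of attendance". Some of them may therefore leave that sensitivity set. The intention-to-treat set is unchanged.

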## 2. Methods

### 2.1. Study Design

The PACO study is a randomized controlled trial setting in public high schools from three Spanish cities (Granada, Jaén, and Valencia), where the schools are the units of randomization, and individuals within the schools are the units of analysis (the participants). The intervention focuses on promoting cycling to school and will be implemented in adolescents during 1 month within the physical education (PE) curriculum classes. Six high schools (i.e., an intervention and a control school in each of the 3 involved cities) will be randomly selected to participate. All study participants will be assessed before and after the intervention period using assessment procedures described below.

The PACO study has been approved by the Review Committee for Research Involving Human Subjects at the University of Granada (Reference: 162/CEIH/2016) and registered with a ClinicalTrials.gov ID: NCT03937336. In addition, the present study protocol has been written in accordance with the Standard Protocol Items: Recommendations for Interventional Trials (SPIRIT) statement (see supplementary file 1).

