## 6. Data Analysis

Descriptive characteristics of the sample will be reported as means and standard deviations for continuous variables, and frequencies and percentages for categorical variables. Analysis of variance and Chi-square tests will be conducted to determine differences in all variables between study group (i.e., control or intervention) at baseline.

Firstly, the appropriateness of the randomization process will be analysed by exploring outlier values and the normal distribution of the variables using the Kolgomorov–Smirnov test and graphical procedures (normal distribution plots). After inspecting outliers and extreme values, these will be winsorized using the 1st percentile and 99th percentile of the distribution of variables.

Secondly, analysis of covariance (ANCOVA) will be used to analyse the main effects of the study group (fixed factor) on cycling to school, ACS, PA levels, SDT-related variables in ACS, and individual, interpersonal, and environment variables related to ACS from the SEM (dependent variables). The effect size between groups will be calculated according to Lipsey and Wilson (2001), with the following formula: r = [t^2^/(t^2^ + gl)], where t = value of the Student t statistic and gl = degrees of freedom. Additionally, to examine change between baseline and post-intervention, regression models will be used, including the study group in the model as fixed factor and the mean difference (post-intervention minus baseline) of outcome variables as dependent variable.

Finally, to analyse the influence of covariates in the association of the intervention and the main outcome (i.e., cycling to school, ACS, and PA levels), mediation analyses will be performed using the PROCESS macro for SPSS (SPSS Inc., Chicago, IL, USA). For these analyses, the intervention will be included as independent variable and main outcomes as dependent (i.e., cycling to school, ACS and PA levels). Mediators that will be analysed are cycling knowledge, cycling skills, basic psychological needs satisfaction in ACS, motivation for ACS, barriers to ACS from adolescents and parents, and peer social support for ACS.

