**Interpersonal**		
Parental sociodemographic data	School name, age, gender, children´s gender, and full postal address	Family questionnaire
Family socioeconomic status	Family income Parental educational level	Family Affluence Scale (FAS) questionnaire [67] Family questionnaire
Parental perceptions	Barriers to allow their children to ACS	Parental Perception of Barriers towards Active Commuting to School (PABACS) questionnaire [68]
Peer social support	Peer social support	Family questionnaire

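### Peer social support is defined as one percentage per school but is planned as a mediator of pupil-level outcomes

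*Protocol article*

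**What the plan says.** Section 4.2.2, item 8, describes the source: "The peer social support to ACS will be self-reported by parents using a question from the School Travel and Safety survey". The parent chooses one of five frequencies. The section then defines the derived variable: "The final variable to analyse will be the percentage of parents at a given school who will respond" that they see such support daily or a few times a week. That is one number per school at each assessment.

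Section 6 states that "mediation analyses will be performed using the PROCESS macro for SPSS", with the intervention as independent variable and cycling, active commuting to school (ACS) and physical activity as dependent variables. The list of mediators ends with "motivation for ACS, barriers to ACS from adolescents and parents, and peer social support for ACS".

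Section 2.1 randomises six schools, one intervention and one control school in each of three cities, and says that "individuals within the schools are the units of analysis". Section 2.2 plans two classes of about 30 per school, 360 pupils in all. Section 6 lists school name among the covariables for the regression models.

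No pupil-level version of peer social support is defined. None of the other listed mediators is defined as a school aggregate.

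**The concern.** A mediation model needs two links: study group to mediator, and mediator to outcome given study group. With individuals as units, the second link should come mainly from differences between pupils in the mediator. A school percentage has no such differences. Any association with the outcome is an association between school averages, and schools differ in many other ways.

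PROCESS, run on a pupil-level file, would accept the variable without complaint. Each school's value would be copied to all its pupils, and the standard errors would be computed as if every copy were a separate observation. The trial could then report peer support as a pathway when the data show only that schools differ. The individual answers that could address the question are collected and then averaged away.

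**Working it through.** **Inputs.** Three cities, two schools each (Section 2.1); two classes of about 30 per school, 360 pupils (Section 2.2); mediator equal to one percentage per school (Section 4.2.2, item 8); mediation by PROCESS, with school name a listed covariable for the regression models (Section 6).

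**Step 1: the plan's own count.** 3 × 2 = 6 schools; 6 × 2 × 30 = 360 pupils, 180 per arm. This reproduces the target sample.

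**Step 2: information in the mediator.** There is one value per school, so at most 6 distinct follow-up values (fewer if schools tie), 3 per arm. The within-school variance is 0, so the within-school correlation is 1. With m = 60 pupils per school, the design effect is 1 + (m − 1) × 1 = 60, and 360 / 60 = 6 effective observations on the mediator.

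**Step 3: degrees of freedom at school level.**
- Group to mediator: 6 − 2 (intercept, group) = 4; two-sided 5% critical t = 2.78.
- Mediator to outcome given group: 6 − 3 (intercept, group, mediator) = 3; critical t = 3.18. Any further school-level or city-level covariate lowers this.

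**Step 4: school as a factor.** Six school indicators have rank 6. Adding a variable that is constant within school leaves the rank at 6. The mediator's coefficient is then not estimable.

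**Step 5: other school-level covariables.** Six schools support at most six school-level coefficients. Intercept, group and mediator take three. Section 6 also lists enrolment, school socioeconomic status, school engagement, population density, city income, cycling lane length and bicycle racks. These are seven school- or city-level variables for the three remaining places.

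**Step 6: what pupil-level regression would do.** A simulation used 6 schools of 60 pupils and 2000 trials per setting, with no effect of group on mediator or outcome and none of mediator on outcome. Mediation was declared when both paths had p < 0.05 in ordinary regression. Two inputs are assumptions, not in the protocol: a between-school SD of 0.3 on the logit scale for parents' answers, and an outcome intraclass correlation (ICC) from 0 to 0.10.

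| Outcome ICC | False mediation, school percentage | False mediation, parent's own yes/no answer |
|---|---|---|
| 0 | 3.2% | 0.6% |
| 0.01 | 9.7% | 0.8% |
| 0.05 | 27.4% | 0.9% |
| 0.10 | 41.3% | 1.2% |

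With the school percentage, the group-to-mediator path was falsely significant in about 84% to 86% of trials. With the parent's own answer it was still falsely significant in about 19%, because those regressions also ignore school clustering.

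**The case against.** **The definition may be loose wording.** Section 4.2.1 also names a percentage as the final variable for usual mode of commuting, which is plainly recorded per pupil. Item 8 might only mean that the answer is dichotomised and the share reported. But item 8 ties the percentage to a given school, and no individual version appears elsewhere. The parallel does not carry.

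**Pooling may be deliberate.** The question asks what others in the neighbourhood do, and pooled parental reports are a legitimate measure of context. This stands in part: moving to individual answers changes the construct to each family's perception. A contextual mediation would still rest on six schools and 3 degrees of freedom, and would not show mediation at the pupil level.

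**Much of the harm comes from ignoring clustering.** This is fair. The high false-mediation rates arise at the larger assumed ICCs, and the redefined variable still needs a model that respects schools.

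**Stronger readings that the documents do not support.**
- A reader might infer that no group difference in this variable could ever reach 0.05. For exact permutation tests the smallest two-sided p is 2/20 = 0.10 unpaired, or 2/8 = 0.25 within city pairs. The plan uses no such test. A t-test of three schools against three can reach 0.05: for example, 20, 21, 22 against 30, 31, 32 gives t = 10 / √(2/3) ≈ 12.2 on 4 degrees of freedom, p < 0.001. Few schools mean low power, not impossibility.
- A reader might add home-school distance to the inseparable school differences. Section 4.2.2, item 11, measures it for each participant, and it is a listed covariable, so its measured part can be adjusted for.
- A reader might see a contradiction in Table 1, which files "Peer social support" under the interpersonal level. That table sorts by level of influence in the social-ecological model, not by unit of measurement.

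**Conclusion.** The point holds. As written, the definition in Section 4.2.2 does not fit the use in Section 6. The limit of six values, the zero within-school variance, the 3 residual degrees of freedom and the non-estimability with school as a factor follow from the design and need no assumption. The simulated error rates depend on the assumed school variation and ICC, and only illustrate how far a naive analysis could mislead.

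The scope is limited. Peer social support is a single item and one of seven listed mediators. The other mediators and the primary effect estimates for cycling, ACS and physical activity do not depend on this definition. A reader might conclude that the whole mediation aim fails; the documents do not support that. The change is worth making because it is cheap and the planned analysis of this mediator is otherwise uninterpretable.

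**What to change.** In Section 4.2.2, item 8, define the analysed mediator as each parent's own response, either the five-level score or yes/no for at least a few times a week, linked to that parent's child. Keep the school percentage only as a description of the school.

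In Section 6, state that the mediation model accounts for school clustering. The redefinition gives the mediator-outcome path within-school information, but the group-to-mediator path remains a comparison of six randomised schools and must be tested as one.

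Cost: one sentence in the variable definition and one on the model. No new data are needed, because the item is answered individually in the Family questionnaire. The parent-child link is already required for the parental barriers mediator. The downside is that the measure becomes a family's perception and no longer a pooled measure of school context.
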